## Abstract

**Background:**

Increasing prevalences of overweight and obesity in children are known problems in industrialized countries. Early prevention is important as overweight and obesity persist over time and are related with health problems later in adulthood. "Komm mit in das gesunde Boot - Grundschule" is a school-based program to promote a healthier lifestyle. Main goals of the intervention are to increase physical activity, decrease the consumption of sugar-sweetened beverages, and to decrease time spent sedentary by promoting active choices for healthy lifestyle. The program to date is distributed by 34 project delivery consultants in the state of Baden-Württemberg and is currently implemented in 427 primary schools. The efficacy of this large scale intervention is examined via the Baden-Württemberg Study.

**Methods/Design:**

The Baden-Württemberg Study is a prospective, stratified, cluster-randomized, and longitudinal study with two groups (intervention group and control group). Measurements were taken at the beginning of the academic years 2010/2011 and 2011/2012. Efficacy of the intervention is being assessed using three main outcomes: changes in waist circumference, skinfold thickness and 6 minutes run. Stratified cluster-randomization (according to class grade level) was performed for primary schools; pupils, teachers/principals, and parents were investigated. An approximately balanced number of classes in intervention group and control group could be reached by stratified randomization and was maintained at follow-up.

**Discussion:**

At present, "Komm mit in das Gesunde Boot - Grundschule" is the largest school-based health promotion program in Germany. Comparative objective main outcomes are used for the evaluation of efficacy. Simulations showed sufficient power with the existing sample size. Therefore, the results will show whether the promotion of a healthier lifestyle in primary school children is possible using a relatively low effort within a school-based program involving children, teachers and parents. The research team anticipates that not only efficacy will be proven in this study but also expects many other positive effects of the program.

**Trial registration:**

German Clinical Trials Register (DRKS), DRKS-ID: DRKS00000494

## Background

Overweight and obesity in childhood are common problems in most industrialized countries for a long time [1]. Data from Germany show an overweight prevalence of 15.4% in children aged 7-10 years, and of 18.6% in children aged 11-14 years [2]. At present, this prevalence remains constant in some parts of Germany [3] as well as in other countries (e.g. Greece [4], Sweden [5]). The relatively short observation periods, however, may not allow ensuring consistency of this trend.

There are various reasons for the rising prevalence of overweight and obesity in children. Besides genetic predisposition [6], lifestyle and behavioral factors need to be considered: little physical activity [7,8], unfavorable nutrition (first of all high caloric food [9-11]), sedentary activities in leisure time, e.g. TV/video watching or using PC/play-stations [12]. Furthermore, the cultural and socio-economic background may play a role in the development of overweight and obesity in children as children with migration background and children who grow up in economically or socially disadvantaged families are more often affected by overweight and obesity [13-16].

Childhood overweight and obesity has been shown to affect physical health [17,18] as well as psychosocial aspects [19]. Efforts to treat them are troublesome and in the long run often ineffective [20].

Overweight and obesity persist over time within childhood [21,22] until adulthood [23,24]. Besides a higher risk of cardiovascular, and metabolic diseases, overweight and obesity in children is related with further consequences [22], e.g. reduced quality of life [19], poorer level of academic achievement [25], decreased self esteem [26]. Thus, prevention of overweight and obesity in children are an important public health issue in most industrialized countries.

Thus, randomized-controlled trials of overweight prevention programs with sufficient statistical power and suitable outcome measures are still needed [27,28]. Possible reasons for missing evidence of efficacy may be inappropriate methods, too short intervention periods, methodological problems (e.g. lack of randomized controlled study design), unsuitable outcome variables [29].

The implementation of childhood prevention programs in schools is promising [30-33]. Possible barriers are low, so that all children can be reached easily. Children spend the main part of their day in schools, and teachers are the personnel qualified in dealing with children as well as considering their age-appropriate needs and competencies. Although from a public health perspective the role of schools for health promotion is very important, high demand in time and resources may impede long term implementation of intervention programs. Furthermore, despite the central role of schools, the familial and socio-economic background of children should not be neglected: there are indications that prevention programs which involve parents are more effective than other programs [34].

The program "Komm mit in das gesunde Boot - Grundschule" (Join the Healthy Boat - Primary School) funded by the Baden-Württemberg Stiftung (Baden-Württemberg foundation) is based on promising experiences of the precursor project "URMEL-ICE" ("Ulm Research on Metabolism, Exercise, and Lifestyle Intervention in Children" [15,35]). URMEL-ICE was a randomized controlled study to investigate the efficacy of an overweight prevention program in children. It was a school-based project implemented in 64 classes (2^nd ^grade) in 32 schools in Ulm and adjacent regions in Germany. URMEL-ICE was a one year intervention with focus on health-promoting behavior change towards an increase in physical activity, a decrease in the consumption of sugar-sweetened beverages, and a decrease in time spent with screen media [16]. As main result of URMEL-ICE, positive effects in the intervention group compared to the control group were observed: statistically significant improvements in children's aerobic endurance [Brandstetter S, Koch B, Berg S, Fritz M, Galm C, Klenk J, Peter R, Prokopchuk D, Steiner R, Wartha O, Wabitsch M, Steinacker JM: A randomized controlled trial on school-based overweight prevention - effects on aerobic endurance, but not on motor skill, Submitted] and tendencies for lower increases in measures of body fat (waist circumference and subscapular skinfold thickness) [16].

The program "Komm mit in das gesunde Boot - Grundschule" includes in addition to the project URMEL-ICE all four levels of primary school and is now distributed on large scale to school teachers in the whole state of Baden-Württemberg by special educated project delivery consultants. The main goal of the present study is the evaluation of the program's intervention in a routine application in large scale. In the following, the program and the Baden-Württemberg Study are characterized in more detail.

## Methods/Design

### Program overview

The program "Komm mit in das gesunde Boot - Grundschule" is a health promotion program for primary school children in Baden-Württemberg, South West Germany, which started in 2009. It is developed, implemented and evaluated by a research team at Ulm University together with a team of experienced teachers. The program supplements the curriculum for primary schools focusing on subjects covering "humans", "nature" and "culture". It is a school-based program to promote healthy lifestyle choices in children, to increase physical, mental, and emotional abilities and, consecutively, to attenuate the increase in body fat and thus to prevent overweight and obesity.

The contents of the program are fully integrated in the school environment: the intervention of the program is implemented in school lessons and during recess (For details see section "Intervention"). A system of particular interested teachers (project delivery consultants) was established to spread the program throughout the state of Baden-Württemberg: it is a federal state of Germany which is situated in South West Germany and has an area of about 35.751 km^2 ^with a population of 10.750.000. All project delivery consultants were trained intensively and thoroughly in the program's concept and materials. Based on these central training sessions, these teachers are able to hold local training courses in their region for further primary school teachers. 30 and 34 primary school teachers were trained and certified as project delivery consultants in 2009/2010 and 2010/2011, respectively. These project delivery consultants recruited and trained 453 and 437 primary school teachers in 2009/2010 and 2010/2011 respectively. The project delivery consultants are reimbursed for her/his work; school teachers receive travel subsidies for training lessons and perform the program as part of their routine work.

The advantage of the system is that teachers are trained by a colleague or other teacher and not by an external expert. This enhances acceptance of the program and facilitates translation into the school environment and enables a higher sustainability [36]. Furthermore, such systems provide local training courses which support participation of the primary school teachers because of short distances. Dissemination is facilitated in a whole state approach with limited resources because the scale-cost effects are much lower than in expert intervention programs [37].

The quality of the program is permanently assessed by process evaluation. Additionally, an investigation of effects of the intervention is being performed in the Baden-Württemberg Study. The study protocol was developed in 2009 and approved by the ethics committee of Ulm University in June 2009 (Application No. 126/10). The study started in 2010 with baseline measurements. Follow-up measurements were carried out in 2011. Furthermore, approval of the Baden-Württemberg Study was obtained from the Ministry of Culture and Education of the state of Baden-Württemberg. The teachers and principals of the participating schools as well as the children's parents gave written informed consent to participate. The Baden-Württemberg Study is registered at the German Clinical Trials Register (DRKS), Freiburg University, Germany, under the DRKS-ID: DRKS00000494.

### Aims of the Baden-Württemberg Study

Three parameters are specified as main efficacy outcomes in the study protocol: change in waist circumference, change in subscapular skinfold thickness and change in endurance performance during a 6-min run; changes are measured as difference between follow-up measurement and baseline measurement. These parameters were chosen because of their reasonably objective measurement and the results of the URMEL-ICE study [16]. Changes in a number of parameters concerning the following topics are regarded as further outcomes as well as influencing factors:

• Children's physical, mental, and emotional "fitness"

• Health related quality of life in children

• Behavior and behavior-related cognition in children and parents

• Children's physical activity behavior

• Socio-demographic parameters of children and parents

• Familial and social anamnesis of children and parents

• Education

• School Environment

• Health-economic aspects

The parameters for the further outcomes were chosen because of its importance for the children's health. Details of the parameters are described in the section "Assessments of the Baden-Württemberg Study".

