### Power considerations

Power calculations were made at beginning of the study based on the availability of data for the main outcome parameters at baseline. Three main outcome parameters for the assessment of efficacy are specified in the study protocol: change in waist circumference, change in subscapular skinfold thickness and change in 6-min run performance, changes are calculated as differences between follow-up measurement and baseline measurement. All power calculations are based on simulations of hypothetic data and application of linear mixed effects models [51,52]. An adjustment according to Bonferroni was made to account for multiple testing [53]. In each mixed effects regression model only group (intervention group vs. control group) was used as explanatory variable and no distinction was made between several classes within the same school. Data from the project URMEL-ICE were used for specifying the differences between intervention group and control group. Randomization data were used for specifying the numbers of schools: IG: n = 44 schools, CG: n = 42 schools. Numbers of baseline measurements available for each primary outcome were used for calculation of pupil numbers in each study group:

• waist circumference: n = 1893 (IG: n = 1038, CG: n = 855)

• subscapular skinfold thickness: n = 1855 (IG: n = 1014, CG: n = 841)

• change in 6-min run performance: n = 1884 (IG: n = 1034, CG: n = 850)

Using this information, the following assumptions were made for the number of pupils in each school:

• change in waist circumference: IG: n = 24 (~1038 pupils in 44 schools); CG: n = 20 (about 855 pupils in 42 schools)

• change in subscapular skinfold thickness: IG: n = 23 (~1014 pupils in 44 schools); CG: n = 20 (about 841 pupils in 42 schools)

• change in 6-min run performance: IG: n = 24 (~1034 pupils in 44 schools); CG: n = 20 (about 850 pupils in 42 schools)

Furthermore, it was assumed that a percentage of 80% measurements available at baseline will be available at the follow-up, too. This percentage is an approximate value and was observed in the project URMEL-ICE.

The simulation results showed that the following values for statistical power could be reached if the assumptions proved right: 85% (change in waist circumference), 76% (change in subscapular skinfold thickness), and 74% (change in 6-min run performance).

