### Statistical considerations

Besides descriptive methods, complex statistical models will be used for statistical analysis of main and further outcomes because of the clustered data structure. For example, mixed effects regression models [52] or GEE models [54] will be used. Both procedures can be extended in an easy way to adjust for possible covariates, e.g. variables regarding the familial and social background of children or time span between time of baseline measurement and time of follow-up measurement.

Health-economic aspects will be evaluated in a similar way as performed for the project URMEL-ICE [37].

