The program is easily feasible by the class teacher and the additional effort required is very low. No external experts and no additional physical education lessons are necessary. An important point is the investigation of efficacy of the intervention which is part of the program: for a lot of other prevention programs efficacy could not be shown [27,28]. For an evaluation of the efficacy of the intervention the Baden-Württemberg Study is performed. It is a prospective, stratified, cluster-randomized, longitudinal study with two groups. Stratified randomization was performed for primary schools in Baden-Württemberg, South West Germany, according to school type (number of classes and grade). Despite withdrawal of written consent from 7 teachers of 5 schools, there is an approximately balanced number of classes in intervention and control group at baseline: within 1^st ^grade classes (39:36), within 2^nd ^grade classes (32:29), and within mixed-grade classes (10:11). Because only three teachers refused written consent after baseline measurements, the approximate balance between schools remained stable at follow-up. At baseline the percentage of boys in both study groups is comparable within 1^st ^grade classes (50.1% and 50.6%) and within mixed-grade classes (58.5% and 58.9%). A difference in this percentage is observed within 2^nd ^grade classes (45.6% and 50.3%). Therefore, an adjustment for sex will be realized in the statistical analysis.

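### The main outcomes are change scores, and the pupil's baseline value of the outcome is not among the covariates named for the analysis

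*Protocol article*

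**What the plan says.** The section on the aims of the study names three main outcomes: change in waist circumference, in subscapular skinfold thickness and in 6-min run performance. It adds that "changes are measured as difference between follow-up measurement and baseline measurement". The section on power considerations repeats this definition.

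For the analysis, the section on statistical considerations says "For example, mixed effects regression models [52] or GEE models [54] will be used". On covariates it says "Both procedures can be extended in an easy way to adjust for possible covariates, e.g. variables regarding the familial and social background of children"; its other example is the time between the two measurements. The Discussion repeats these examples and makes one firm commitment, prompted by a difference in the share of boys among 2nd-grade pupils (45.6% against 50.3%): "Therefore, an adjustment for sex will be realized in the statistical analysis". None of these places names the baseline value of the outcome.

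A model with no covariates appears only under power considerations: "In each mixed effects regression model only group (intervention group vs. control group) was used as explanatory variable". That sentence concerns the simulations: "All power calculations are based on simulations of hypothetic data and application of linear mixed effects models". On multiplicity the section says "An adjustment according to Bonferroni was made to account for multiple testing". The stated power is 85% (waist), 76% (skinfold) and 74% (6-min run).

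The section on the status of the study reports that follow-up is complete and that statistical analysis has not begun.

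**The concern.** A change score fixes the coefficient of the baseline value at 1. Adjusting for baseline lets the data estimate that coefficient. Unless the true slope of follow-up on baseline happens to be 1, the change score carries avoidable variance, and any baseline difference between arms feeds partly into the estimated effect.

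Three features make this matter here:

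- Two of the three main outcomes have stated power below 80%.
- Schools withdrew unevenly straight after randomization: 1 in the intervention group and 4 in the control group, the latter because of their allocation. Some baseline imbalance is therefore possible, although the article shows no baseline means of the outcomes.
- The article adjusts for sex because of an observed difference between arms. The same reasoning applies at least as strongly to baseline waist, skinfold and run distance, which bear directly on the outcomes.

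If the choice between unadjusted change and a baseline-adjusted model stays open until the data are analysed, it becomes a post-hoc choice on three primary tests.

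**Working it through.** **What can be reproduced.** The stated power cannot be: the article gives no effect size, SD, intraclass correlation (ICC), overall alpha or sidedness. The pupils-per-school inputs can be checked and agree:

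- waist: 1038/44 = 23.6 (24) and 855/42 = 20.4 (20)
- skinfold: 1014/44 = 23.0 (23) and 841/42 = 20.0 (20)
- 6-min run: 1034/44 = 23.5 (24) and 850/42 = 20.2 (20)

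**Assumptions.** Let r be the baseline to follow-up correlation and k the ratio of follow-up SD to baseline SD. Neither is in the article, so ranges are shown. Alpha is taken as two-sided 0.05/3. The baseline slope is taken as the same within and between schools.

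**Variance.** In units of the baseline variance:

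- change score: 1 + k² - 2rk
- baseline-adjusted: k²(1 - r²)
- difference: (1 - rk)², which is never negative

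In large samples, then, the change score is never the more precise of the two, and they tie only when rk = 1. With equal SDs (k = 1) the ratio of adjusted to change-score variance is (1 - r²)/[2(1 - r)] = (1 + r)/2. That is 0.95, 0.90 and 0.85 at r = 0.9, 0.8 and 0.7.

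**Power with equal SDs.** The implied signal-to-noise ratio is z(1 - 0.05/6) + z(power):

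- waist: 2.394 + 1.036 = 3.430
- skinfold: 2.394 + 0.706 = 3.100
- 6-min run: 2.394 + 0.643 = 3.037

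Adjusted power is Φ(ratio/√((1 + r)/2) - 2.394).

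| Outcome | Stated | r = 0.9 | r = 0.8 | r = 0.7 |
|---|---|---|---|---|
| Waist | 85% | 87.0% | 88.9% | 90.8% |
| Skinfold | 76% | 78.4% | 80.9% | 83.4% |
| 6-min run | 74% | 76.5% | 79.0% | 81.6% |

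At r = 0.95 the gain is about one point for each outcome.

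**Sensitivity to the SDs.** Suppose the follow-up SD is 10% larger (k = 1.1). The variance ratios become:

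- r = 0.9: 1.21 × 0.19 / (2.21 - 1.98) = 0.2299/0.23 = 0.9996
- r = 0.8: 1.21 × 0.36 / (2.21 - 1.76) = 0.4356/0.45 = 0.968
- r = 0.7: 1.21 × 0.51 / (2.21 - 1.54) = 0.6171/0.67 = 0.921

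Power for the 6-min run would then be about 74.0%, 75.6% and 78.0%.

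**Bias and imbalance.** With equal SDs and a baseline difference b (intervention minus control), the change-score estimate shifts by -(1 - r)b. For b = 0.1 SD this is -0.05 SD at r = 0.5, -0.03 SD at r = 0.7 and -0.01 SD at r = 0.9. An intervention arm that starts higher would thus appear to gain less waist or skinfold with no true effect.

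**Simulation check.** I ran 3000 trials at each r, with 44 and 42 schools, 19 and 16 pupils per school after 80% retention, an assumed ICC of 0.03, equal SDs, no true effect, and baseline adjustment by least squares. The variance ratios were 0.755, 0.864, 0.948 and 0.975 at r = 0.5, 0.7, 0.9 and 0.95, against 0.75, 0.85, 0.95 and 0.975 from the formula. The mean change-score estimate lay between -0.0007 and 0.0005 SD, so there was no bias on average. Chance baseline imbalance had an SD of about 0.06.

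**The case against.** The strongest reply is that this is an unnamed covariate, not an error. The covariates are given as examples, nothing rules the baseline value out, and a condensed article may leave the final list to an analysis plan that is not shown. A change-score response is also fully compatible with baseline adjustment. All of this stands, and it rules out any claim that the plan rejects baseline adjustment. The point that remains is narrower: the article fixes the outcomes as change scores and discusses covariates more than once without mentioning the baseline value, which is the one most directly tied to that choice.

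Several stronger readings are tempting but not supported:

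- **That the arms will be compared by group alone.** The group-only model belongs to the power simulation. The analysis is committed to sex and allows for more covariates.
- **That regression to the mean biases the result.** Under school randomization the difference in change is unbiased on average. Regression to the mean enters only conditionally, through a baseline difference.
- **That imbalance is shown.** The roughly 55:45 split of measured pupils (1038:855 for waist) is a headcount, partly explained by 81 against 76 classes. The article does not date parental consent relative to randomization, so one cannot say outright that pupils joined after allocation.
- **That adjustment would cure selection.** It deals with chance imbalance in the measured baseline value; it does not guarantee removal of selection bias.
- **That the power gain is established.** It depends on r, the SD ratio and alpha, none of which is stated.

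**Conclusion.** The point holds as an improvement to the analysis, not as a demonstrated bias or a contradiction. The main outcomes are change scores, and the baseline value is absent from the covariates the article names. Adding it does not reduce large-sample precision, and it removes the dependence of the estimate on chance baseline imbalance.

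The size is modest and uncertain. With equal SDs and r between 0.7 and 0.9, the variance falls by 5% to 15% and power rises by about 2 to 8 points across the three outcomes. With a follow-up SD 10% larger and r = 0.9, the gain is practically nil. These figures rest on the assumed r, SD ratio, two-sided alpha of 0.05/3 and common baseline slope within and between schools.

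**What to change.** Before analysis starts, specify the primary model for each of the three outcomes as a linear mixed model with a random effect for school and fixed effects for group, the pupil's baseline value of that outcome, and sex as already promised. The response may be follow-up or change, because with baseline in the model the group coefficient is the same. Name the adjusted between-group difference as the primary estimate and report unadjusted change descriptively. If an analysis plan already says this, confirming it is enough.

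The cost is a sentence or two in the analysis plan. Both measurements are already needed to compute the change, so no further data are required.
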